### Hypotheses

We hypothesized that, compared to the waiting list control group, both MBHC and MBHC-VR will improve occupational indicators (Hypothesis 1), mental health (Hypothesis 2), and psychological functioning (Hypothesis 3). We expect that, compared to MBHC, MBHC-VR will have higher adherence to home practice [5], and result in greater magnitude of change in the occupational balance, mental health and psychological functioning variables (Hypothesis 4). Furthermore, we expect that improvements will be maintained at 3-months post-intervention completion [5] (Hypothesis 5). Finally, we predict that psychological functioning variables will act as mechanisms of change of occupational balance and mental health indicators in experimental vs control condition [35] (Hypothesis 6). All hypotheses will be tested in the post-training assessment, except for hypothesis 5, which will be tested in the follow-up.

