### Intervention groups

#### Mindfulness-Based Health Care Program (MBHC)

The MBHC program is adapted for university students from the Mindfulness-Based Stress Reduction (MBSR) program [40]. MBSR is an 8-week evidence-based program that cultivates mindfulness of present-moment and a nonreactive, nonjudgmental attitude toward the experience. This version of the MBHC program [36] will be offered in-person and has a similar structure to the MBSR program but is focused for university students and introduces elements related to healthy habits and lifestyle. Features of MBHC that differ from MBSR will include: a) 6-weeks instead of 8-weeks of group instruction; b) weekly 1.5 hours sessions instead of 2.5–3 hours; and c) specific formal and informal practices aimed at cultivating healthy habits and lifestyle (e.g., activities of daily living such as feeding, bathing or showering and other occupations such as communication management, health management, etc. [41]; and prosocial components (e.g., kindness and compassion).

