Core components of MBHC include: a) paying attention to the present moment; b) cultivating acceptance and openness to the present experience, without resistance and judgment; c) developing and strengthening prosocial qualities, such as kindness and compassion; d) enhancing deep self-inquiry by examining subjective experience of thoughts, feelings, and sensations; and e) promoting healthy habits and occupations. We will also include person-centered facilitation techniques, which include: 1) Unconditional positive regard; 2) Empathy; 3) Authenticity in interactions; 4) Client-centered focus; 5) Non-directive approach; 6) Self-actualisation; 7) Reflection and clarification; 8) Non-judgmental listening; 9) Holistic approach; and 10) Emphasis on the “Here and Now”; [42] and non-violent communication practices (Observation of the situation, Recognition of feelings, Identification of needs, Formulation of clear requests) [43] to support a conducive learning environment and facilitate communication. All sessions will include mindful movement, formal and informal meditation practices, sharing personal experiences and thoughts, and exercises to do at home. At the end of each session, participants will receive a set of pre-recorded audio files and printed material to support their daily practices. The structure of the MBHC program sessions is included in *S1 Appendix*. Additionally, as an example, the material of the first session is available on the web page of the B+D+b Occupational Research Group of the Miguel Hernández University.

MBHC and MBHC-VR programs will be conducted by two instructors, both with over 25 years of experience in Tibetan, Theravada and Zen meditation; experience in retreats of weeks and months in the West and Sri Lanka, and with more than 15 and 8 years of experience, respectively, facilitating mindfulness-based programs. The program has been previously implemented at Miguel Hernández University of Elche since 2016, involving university students.

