*Marlowe-Crowne Social Desirability Scale* short form (M-C SDS Scale) [54] consists of 18 items, 13 items reflecting very frequent undesirable behaviours and traits, and other 5 items reflecting infrequent socially desirable behaviours and traits. The person being assessed must indicate whether they are true or false with regard to him/herself. The sum of the scores gives a total score between 0 and 18, where a higher score indicates a higher social desirability, understood as a response bias or personality trait. It internal consistency is 0.76.

*Mediterranean Diet Adherence Test* [55] is a brief dietary assessment consisting of 14 questions that evaluates adherence to the Mediterranean Diet pattern. This questionnaire scores one point per question, with a score of <9 meaning low adherence and a score of > = 9 meaning good adherence.

*Insomnia Severity Index* (ISI) [56] is a 5-item self-report instrument that assesses the severity of the sleep problem, the degree of dissatisfaction and the impact on quality of life. Scores range from 0 (best score) to 28 (worst score). The internal consistency of this instrument is 0.82.

*International Physical Activity Questionnaire* short form (IPAQ-SF) [57] is a self-administered questionnaire consisting of 7 items that assesses the time spent being physically active in the last 7 days. The internal consistency of this assessment tool is 0.337.

*Plymouth Sensory Imagery Questionnaire* (Psi-Q) [58] measures vividness of mental imagery and consists of 21 items measuring 7 sensory modalities: vision, sound, smell, taste, touch, bodily sensation and emotions. The questionnaire has a Likert-type scale between 1 (no imagery) and 7 (perfectly clear and as vivid as the actual experience). The internal consistency of this instrument is 0.88.

*Intervention adherence*. During weeks 1–6 of MBHC program, adherence will be recorded by means of: 1) class attendance, 2) number of minutes practicing mindfulness each day (question number 11 of the EMA). In the follow-up period (weeks 7–18) participants will receive a weekly survey asking for the frequency (number of days per week) and duration of mindfulness practice (minutes) during the last week [59].

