*Ecological momentary assessment*. This evaluation "at the moment" and "in the current context" presents multiple methodological advantages compared to traditional data collection systems: 1) it reduces memory bias by obtaining current or recent experience information; 2) allows the collection of information in the environment of the subject, increasing compliance and reliability; 3) and allows the detection of variations over time and factors that influence the evolution of the participants [34]. Our EMA will include 11 questions (Table 2) assessing occupation (question 1), volition (question 2), mindfulness state (question 3), well-being state (questions 4 and 9), positive and negative affect of high and low arousal (questions 5 and 6), state stress (question 7), self-compassion (question 8), recovery experience (question 10) and monitoring of daily mindfulness practice (question 11). Questions 2 to 11 will be answered using a visual analogue scale from 0 to 10 points.

**Table 2 pone.0302018.t002:** Questions included on Ecological Momentary Assessment (EMA).

1. What are you doing right now?
2. This activity is motivating for me
3. I was thinking about something other than what I was doing right now
4. What is my mood right now?
5. I have felt happy and in a good mood while doing that activity
6. I have felt calm and relaxed while doing that activity
7. What is my stress level right now?
8. While doing the activity, have I given to myself the care and kindness that I need?
9. What is my level of happiness right now?
10. In the last 24 hours I have carried out some recovery activity/experience (I have slept well, I have played sports, leisure activities, etc.)
11. In the last 24 hours, how many minutes have I spent practicing mindfulness?

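### EMA question 11, the only measure of practice minutes in weeks 1–6, does not exclude the weekly class, whereas Hypothesis 4 concerns home practice

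*Protocol article*

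**What the plan says.** The Hypotheses section states: "compared to MBHC, MBHC-VR will have higher adherence to home practice". All hypotheses except the fifth are to be tested at the post-training assessment, so this clause rests on what is collected during the six weeks of the program.

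The paragraph on intervention adherence says that in weeks 1–6 "adherence will be recorded by means of: 1) class attendance, 2) number of minutes practicing mindfulness each day (question number 11 of the EMA". The EMA paragraph gives the purpose of the item as "monitoring of daily mindfulness practice (question 11", and Table 2 prints its wording: "In the last 24 hours, how many minutes have I spent practicing mindfulness". The Measures section fixes one prompt a day, in the early evening.

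The section on the MBHC program describes "weekly 1.5 hours sessions instead of 2.5–3 hours", over six weeks, and says of their content: "All sessions will include mindful movement, formal and informal meditation practices". The MBHC-VR section places VR practice both in the session and at home. Nowhere does the protocol tell participants to leave class time out of question 11, or say that class time will be subtracted.

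In weeks 7–18 a weekly survey asks about days and minutes of practice. There are no classes in that period.

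**The concern.** The hypothesis names home practice. Of the two adherence measures in weeks 1–6, attendance is not home practice, so the clause depends on question 11. As printed, question 11 asks for all mindfulness practice in a 24-hour window, and once a week that window contains a class in which mindfulness is practised. A student who answers literally will include it.

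What is at stake is the reading of the adherence clause of Hypothesis 4. If VR students attended more classes but practised no more at home, question 11 could still show a VR advantage. If attendance were equal, a real advantage would look smaller in relative terms than it is. The Introduction offers VR as a way to improve home practice and adherence, so it matters which of these a result reflects.

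**Working it through.** The protocol states no figure here to reproduce. The check has two parts: which prompts are affected, and how class minutes pass into the comparison between arms.

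**Prompts affected.** One prompt a day for six weeks gives 6 × 7 = 42 prompts. One class a week gives 6 windows that contain a class, and 6/42 = 1/7. The other 36 contain no class and, as worded, already measure out-of-class practice. If a class overlaps the prompt time, it can fall into two windows, so the count could be somewhat higher.

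**Model.** Let c be practice minutes in one class, h home minutes per week, and a the attendance rate. If every prompt is answered literally, the expected weekly total is h + a·c. The difference between arms is

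(h_VR − h_MBHC) + (a_VR − a_MBHC)·c.

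The second term is the error. It is zero when attendance is equal.

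**Inputs.**
- Class length: 90 minutes weekly (MBHC section).
- c = 30–60 minutes of actual practice per class: assumed.
- h = 60–120 minutes per week: assumed.
- Attendance gap = 16–30 percentage points: assumed. The range is borrowed from the Introduction, which cites adherence 16% to 30% higher with VR in an earlier trial. That figure is for adherence, not specifically for class attendance.

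**Class share of a full attender's weekly total, c/(c + h).**
- Lowest: 30/(30 + 120) = 20%.
- Highest: 60/(60 + 60) = 50%.

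**Unequal attendance, equal home practice: false difference = gap × c.**
- Lowest: 0.16 × 30 = 4.8 minutes per week, or 4.8/120 = 4% of home practice.
- Highest: 0.30 × 60 = 18 minutes per week, or 18/60 = 30% of home practice.

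**Equal full attendance, true home ratio of 1.30 (illustrative): observed ratio = (1.30h + c)/(h + c).**
- c = 60, h = 60: (78 + 60)/120 = 1.15.
- c = 30, h = 120: (156 + 30)/150 = 1.24.
- The absolute differences stay at 18 and 36 minutes, as they should.

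**After the change.** With class minutes excluded by wording, or class windows left out, the term in c disappears and only the difference in home practice remains.

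**The case against.** The strongest reply is that question 11 was meant to cover practice between classes. Attendance and daily minutes are listed as separate indicators, and the protocol speaks of daily practice when describing the take-home audio and printed material. Form instructions or a briefing, which are not shown, may have told students to leave class out. This reading is possible, but the printed item does not say it. An analysis plan cannot change what respondents were asked; it can only discard the affected days.

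Several other objections stand and limit the point:
- A reader might infer that home practice cannot be recovered. The documents do not support that: the item is daily and classes are weekly, so about 36 of 42 prompts are unaffected.
- A reader might infer that attendance is counted twice. No section combines attendance and minutes into one score.
- A reader might infer an artificial fall in practice when classes end after week 6. No planned analysis of practice minutes across the EMA and the later weekly survey is described, and Hypothesis 4 is tested at post-training.
- Absolute bias needs unequal attendance, and the protocol gives no attendance data. The two programs share content and objectives.
- Giving the whole 16–30 point gap to attendance while holding home practice equal is the unfavourable case, and it assumes that every class-day prompt is answered.

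The protocol also says questions 2 to 11 use a 0–10 visual analogue scale, which does not fit an item asking for minutes. That is a separate defect of the same item. Until it is settled, the minutes above are only illustrative; settling it would not remove class time from the answer.

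**Conclusion.** The point holds in limited form. As printed, question 11 does not isolate the construct named in Hypothesis 4, and nothing in the protocol excludes class minutes. That they are counted is an inference from the unrestricted wording, not something the protocol states.

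The mixing is confined to about one prompt in seven. With unequal attendance it biases the MBHC-VR versus MBHC comparison of home practice; under the assumed values the false difference is about 5–18 minutes per week. With equal attendance the absolute difference is unaffected, and a ratio of 1.30 would appear as about 1.15–1.24. These figures show what is possible, not what is likely, because the protocol gives neither class nor home practice minutes.

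Adherence is listed as a secondary outcome and is one clause of Hypothesis 4. The main outcomes, the outcome-change part of Hypothesis 4 and the sample size are untouched. The change is still worth making because it costs almost nothing.

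**What to change.** Add the words 'outside the class sessions' to question 11. Keep class attendance as a separate measure, and state that the adherence part of Hypothesis 4 is tested on out-of-class minutes. The weekly survey for weeks 7–18 can stay as it is.

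For editions already run with the present wording, leave out the EMA windows that contain a class. Define them by the scheduled class date and apply the rule to everyone in both arms. Defining them by individual attendance would remove days only from attenders and make the days analysed depend on behaviour after randomisation. Where a class overlaps the prompt time, leave out both windows. Report the result as minutes per non-class day, since home practice on class days is also lost.

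The cost is a few words in an online form and, for past editions only, about one day in seven of the practice data.

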#### Qualitative assessment

We will conduct focus groups with all participants in the MBHC and MBHC+VR arms of the trial.

During the focus groups, we will ask questions to elicit a deeper understanding of participants’ experiences, considering that group interactions can trigger responses and generate insights that may not emerge during individual interviews. Each focus group will occur within 2 weeks of MBHC completion and will be carried out by two researchers (a moderator and an assistant who will be in charge of logistical issues, and will take written notes of aspects that occur during the focus groups).

The participants will be distributed in groups of between 3 and 8 participants, segmented by type of intervention received during the trial, and by gender, since it has been described that carrying out focus groups with people of the same gender generates greater quantity and depth in the answers. Escobar and Bonilla-Jimenez recommend having a homogeneous group if the study aims to gather information that comes from shared experiences [60].

This technique will be carried out by means of a flexible script of open questions (Table 3) by experts in the subject of study, but unknown by the participating subjects, and will be recorded by means of voice recording devices. Focus groups will continue until no new issues are identified, which will suggest data saturation. The information obtained in these focus groups will be organized into meaningful patterns in order to draw conclusions.

**Table 3 pone.0302018.t003:** Thematic guide for focus group discussions.

How did you feel during the mindfulness sessions? And after the sessions, have you noticed any changes?
Have you noticed any positive effects that you associate with carrying out the mindfulness program? Have you noticed any negative effects that you associate with carrying out the mindfulness program or the use of virtual reality?
What problems have you had to attend the sessions? And to do it at home?
What aspects make it easier for you to attend the sessions? What aspects make it easier for you to do it at home?
Are you satisfied with the program? What aspects did you like the most? Which ones did you like the least, or what would you change about the program to improve it?
Which of your expectations have been met? Which ones don’t?

### Adverse events and safety considerations

The scientific literature on meditation-associated adverse events [MRAEs] is sparse and contradictory. However, some recent studies have suggested that MRAEs do occur in these meditation-based interventions, including those that focus on mindfulness [61–63]. According to a recent meta-analysis [64], the prevalence of MRAEs in experimental studies is 3.7% (95% CI = 0.02–0.05). The most frequent MRAEs were anxiety, depression and cognitive abnormalities (e.g. thought disorganization), stress and hallucinations and, normally, they appeared during or immediately after the practice [64].

On the other hand, regarding VR, scientific evidence shows disorientation followed by nausea and oculomotor disturbances as the most frequent negative effects, although their magnitude seems to be conditioned by factors such as the socio-demographic characteristics of the users, the VR content (neutral versus exciting) and the exposure time (adaptation after repeated exposures and greater orientation in exposures equal to or greater than 10 minutes) [65].

In this clinical trial, the participants will be encouraged to report any adverse events occurring during practice as soon as possible by WhatsApp or in-person during class. Any adverse events will be reported by the principal investigator to the Research Ethics and Integrity Committee of the Miguel Hernández University using an adverse event report. Additionally, should any participants require psychological or psychiatric treatment during the study, they will be excluded and referred to specialized care services.

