#### Waiting list control group (WL)

Participants in the WL control group will not receive any intervention during the study. However, for ethical reasons, at the end of the 3-month follow-up assessment, participants of this WL control group will be invited to participate in the MBHC program free of charge.

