In this study, special attention is also paid to the possibility of adverse effects associated with the practice of meditation, as evidenced by previous studies [64, 88, 89]. In anticipation of this, the participants will communicate to the research team any difficulty or symptomatology that may arise, in order to attend to and solve these events as quickly as possible and, if necessary, refer the participant to the specialized psychological services available at the university. Likewise, participants will also report possible adverse effects during and/or after VR exposure. In the MBHC-VR group of this research, VR with neutral and pleasant contents will be used in all sessions for a time between 10 and 15 minutes, favoring adaptation to the exposure and minimizing possible adverse effects.

It is also worth mentioning that the programs will be implemented by a multidisciplinary professional group with extensive experience in university education and highly qualified in MBIs. In this sense, the team is made up of occupational therapists, psychologists, physiotherapists, mindfulness experts and university professors’ experts in teaching and research.

In terms of feasibility, face-to-face interventions will be carried out in groups of about 15 people, who can be attended simultaneously, thus being a low-cost community mindfulness program for university students. If the MBHC programs designed for this study are effective, one of the advantages is that their applicability can be extended to other universities. Also, the materials and procedures will be available to the educational and scientific community. Thus, the range of effective interventions available to address university students’ mental health will be expanded.

The present trial can also contribute to expanding knowledge on personalized treatments. Baseline characteristics of individuals have started to be used as predictive factors of differential response to intervention strategies. This study will allow identifying individuals within the included sample that will benefit more from utilizing one condition relative to the other. It will also allow to establish moderating mechanisms of efficacy.

In short, and from the point of view of clinical practice, it is expected that with the proposed intervention university students will learn to relate in a healthier way with their mental processes, so as to improve their OB and their psychological well-being.

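### The adverse event rule is narrower than the protocol's own account of the risk, does not fit the waiting list, and is backed by no harms question common to all three arms

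*Protocol article*

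**What the plan says.** The section on adverse events and safety sets the collection rule: "the participants will be encouraged to report any adverse events occurring during practice as soon as possible by WhatsApp or in-person during class". In its background on meditation-related events, the same section says that "normally, they appeared during or immediately after the practice".

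The Discussion describes reporting more widely. It says that "the participants will communicate to the research team any difficulty or symptomatology that may arise", and then that "participants will also report possible adverse effects during and/or after VR exposure".

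One solicited question on harm appears under Qualitative assessment. The focus group guide (Table 3) asks: "Have you noticed any negative effects that you associate with carrying out the mindfulness program or the use of virtual reality". On who is asked, the text says: "We will conduct focus groups with all participants in the MBHC and MBHC+VR arms of the trial". The groups meet within two weeks of programme completion and continue until saturation.

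Waiting list participants "will not receive any intervention during the study". They do receive the daily EMA form during the six weeks (Measures). Its 11 questions (Table 2) include mood and stress ratings but nothing on unwanted effects. For the later period, the adherence paragraph says: "In the follow-up period (weeks 7–18) participants will receive a weekly survey asking for the frequency (number of days per week) and duration of mindfulness". It gives no safety content for that survey. Table 1, presented as showing all the measures used at each time point, lists no adverse event measure.

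**The concern.** The sentence that governs collection is the narrowest of the statements on reporting. A participant who follows it literally would not report a symptom that begins after the session or after the headset comes off. Yet the protocol itself says that events also begin then.

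The rule also presupposes an exposure that the waiting list does not have. Anxiety, depression and stress are among the most frequent events named in the safety section. The Introduction cites student prevalences of 34% for depression and 32% for anxiety. Without the same question in the waiting list, a count of such events in the programme arms cannot be separated from what students would have reported anyway. Where reporting depends mainly on participants coming forward, few reports may mean few events or little reporting. The Discussion says that special attention is paid to adverse effects, so the counts are likely to be read as evidence on safety.

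**Working it through.** The point rests on text. The plan states no harms figure to reproduce, so the routes are set side by side first and the arithmetic then gives the scale.

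| Route | Arms reached | When | What it asks about harm |
|---|---|---|---|
| Volunteered report (safety section) | Those who practise or attend class | WhatsApp: no end stated. Class: the six programme weeks | Events during practice |
| Volunteered report (Discussion) | No arm named; the context is meditation and VR | No limit stated | Any difficulty or symptom; effects during or after VR |
| Daily EMA form | All three | Weeks 1–6 | No harms question; mood (item 4) and stress (item 7) are rated |
| Weekly survey | Arm not stated | Weeks 7–18 | Days and minutes of practice only |
| Focus groups | MBHC and MBHC-VR | Once, within two weeks of completion | Negative effects that the participant links to the programme or VR |
| DASS-21 | All three | Pre, post, follow-up | Past-week anxiety, depression and stress, not logged as adverse events |

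**Window.** The safety rule covers events during practice. The background in the same section covers during or immediately after. The Discussion sets no limit for general symptoms and covers during or after for VR. These statements disagree, and the governing one is the narrowest.

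**Arms.** No row combines all three arms with a question about adverse events. The two rows that reach all arms with symptom content (EMA and DASS-21) do not measure thought disorganization, hallucinations, disorientation, nausea or oculomotor disturbance, all of which the safety section names.

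**Time.** Weeks 7–18 are 12 of the 18 weeks. In that period no regular form is described as asking about harm. The focus groups fall at its start.

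**Scale.** Inputs: prevalence 3.7%, with the cited interval 0.02–0.05 read as 2% to 5% (safety section); 70 per arm (Sample size estimation).

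- Expected events per programme arm, n × p: 70 × 0.037 = 2.59. Range: 70 × 0.02 = 1.4 to 70 × 0.05 = 3.5.
- Both programme arms: 140 × 0.037 = 5.18.
- Chance of no event in an arm even if every event is captured, (1 − p)^n: 0.963^70 = 0.071. At 2%, 0.98^70 = 0.243. At 5%, 0.95^70 = 0.028.
- Power to detect a doubling between two arms of 70, two-sided 5%, normal approximation Φ((Δ − 1.96 × SE0)/SE1). With 7.4% against 3.7%, Δ = 0.037, SE0 = √(2 × 0.0555 × 0.9445/70) = 0.0387 and SE1 = √((0.074 × 0.926 + 0.037 × 0.963)/70) = 0.0386. This gives Φ(−1.007) = 0.157, about 16%. Starting from 2% it is about 10%, and from 5% about 20%.

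So even perfectly equal collection would support only a descriptive comparison.

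**The case against.** The strongest reply is that the article offers more than one sentence on harms, and much of that reply stands. Several stronger readings are tempting, and the documents do not support them.

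- *Harms are collected only by spontaneous report.* Not so: the focus group guide asks both programme arms directly. That question does not fill the gap, however. It is asked once, in a group, about effects that participants themselves attribute to the programme or VR. It yields themes rather than counts, and it may not reach everyone if groups stop at saturation.
- *After-practice events are excluded altogether.* This holds for the safety section's sentence, not for the whole article, because the Discussion is wider. The defect is that the two disagree.
- *The waiting list can report nothing.* Too strong: the Discussion says participants without naming an arm, although its context is meditation practice.
- *Harms cannot be compared between arms.* Too broad: DASS-21 and the EMA mood and stress items allow worsening to be compared across all three arms, and the two programme arms share reporting routes.
- *The VR arm gets an extra prompt.* This is inference. The VR sentence follows a general one, and no separate form or prompt is described.
- *Reporting closes after week 6.* Only the class route ends; WhatsApp is not said to close.
- *Under-reporting can be quantified.* The documents give no capture rate, so any figure would be an assumption.

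It can also be said that a condensed article leaves the adverse event form to the full protocol. That is fair for the form's layout, and its absence here is not a fault. It does not answer a rule that the article does state and that conflicts with the article's own text, nor survey and EMA content that the article spells out. Finally, no hypothesis plans a between-arm test of harms. This limits the weight of the point, but descriptive counts still need equal collection to be interpretable.

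**Conclusion.** The concern holds in a limited form. The stated rule is narrower than the protocol's account of when events occur and narrower than its Discussion. It does not fit the waiting list, and no adverse event question common to all three arms is described. Followed as written, it gives incomplete and unequal harms data: programme-arm counts cannot be set against background, and a low count is not evidence of safety.

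The numbers involved are small. About 2.6 events are expected per programme arm of 70 (1.4 to 3.5 over the cited interval). There is a 7% chance of seeing none in an arm even with full capture (24% at a prevalence of 2%, 3% at 5%). These figures assume that the cited prevalence applies to this population and to these programmes. The efficacy analyses are unaffected. This is a worthwhile, inexpensive improvement rather than a flaw that undermines the trial.

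**What to change.** 1. Reconcile the safety section with the Discussion on one reporting window that is not limited to the time of practice, and state that it applies to all three arms.
2. Add one identical yes/no item with free text on unwanted effects, asked weekly in every arm. Attach it to one EMA form per week in weeks 1–6, and to the weekly survey in weeks 7–18, with that survey sent to the waiting list too. This gives 6 + 12 = 18 askings per participant. A weekly item is preferable to a daily one, which would prompt more symptom reports.
3. Report events descriptively by arm, with solicited and spontaneous reports shown separately, and without a claim of safety from a low or zero count.

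The cost is an amendment and one extra item on two online forms already planned, plus sending the later survey to the waiting list if it does not already go there. The forms become slightly longer, and more minor events have to be logged. The item will prompt some symptom reports, but the prompt is the same in every arm.
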